### Trial duration

The project will take 3.5 years. Patient recruitment will take place over the first 30 months, and collection of data will continue until 42 months.

### Sample size

The power analysis has taken into account the inclusion of a futility analysis to be undertaken after recruitment of one-third of the target sample. We have assumed that the proportion of participants showing a two-point improvement (or greater) on the ASIA Impairment scale will be approximately 0.5 (50%) in the control arm and a minimum of 0.75 (75%) in the intervention arm, based on available data from epidemiological studies.^2^
^7^ The sample size calculation is based on the conservative assumption of no correlation between repeated measures. Under these assumptions, 76 patients per group will provide 90% power and 5% type II errors for a two-sided test. The sample size will be inflated for attrition; on the basis of our experience and the design which minimises loss to follow-up, we estimate 10% attrition. This requires a recruitment of 170 patients (85 participants per arm).

The ASIA total motor score (0–100) is a secondary outcome. Stata ‘*sampsi*’ indicates that using an Analysis of Covariance with a baseline to end point correlation of 0.6, there will be 87% power to detect a difference between the control and treatment arms of a medium to large effect size of 0.4. Such a difference will be of clinical significance.

### Recruitment plan

TM has an estimated UK incidence of 350/year, and the study centres cover approximately half of the UK population. Assuming a recruitment rate of 39% over a period of 2.5 years, we would expect to recruit 170 patients. This recruitment rate is based on a patient and public consultation within the TM society, given that patients will be admitted with a devastating weakness, and the control arm will be receiving standard intervention.

### Randomisation

Prior to randomisation but after consent, site staff will register a recruit on the web-based electronic data capture system (InferMed MACRO), hosted at the King's Clinical Trials Unit (KCTU). Each will be assigned a unique study patient identification number (PIN) by the system. Once baseline assessments are complete, the trained trial staff will access the KCTU randomisation system and randomise the patient at the individual level using stratified block randomisation by service type (adult or child); the block will randomly vary in size. Treatment allocation will be at a ratio of 1:1. Randomisation will occur during office hours when IVIG is available. Patients eligible for trial recruitment presenting outside of these times will be started immediately on IVMP and then randomised at the first available opportunity.

### Blinding

Owing to the technical challenges of masking IVIG from saline, the need for rapid recruitment and the fact that follow-up will be many months after the event using objective, well-defined clinical end points, treatment will not be blinded. Staff carrying out study assessments and statistical analyses will be blinded to intervention.

### Data collection methods

The Kurtzke neurological examination, ASIA Impairment Score, ASIA Motor and Sensory Score and EDSS scores will be completed, together with the treatment, discharge and follow-up forms (see figure 1). All assessments should ideally be performed by the same blinded assessor, who may be a study physician, physiotherapist or research nurse. All assessors will have successfully completed ASIA and EDSS online training modules (further information is detailed in online supplementary appendix 1). Biological samples will be collected, processed and stored as detailed in online supplementary appendix 3.

**Figure 1 BMJOPEN2015008312F1:**
[figure not shown]
Flow chart showing the process of patient recruitment, treatment and follow-up.

### Withdrawal

Patients may withdraw at any time. All withdrawals from randomised treatment will be reported. If consent is given, any existing data or samples will be retained, and follow-up data will continue to be collected; if not, then a withdrawal form will be completed. The investigator may withdraw patients from the study drug in the event of intercurrent illness, AEs, SAEs and SUSARs, subsequent evidence of a different aetiology, protocol violations, cure, administrative or other reasons. All data will be analysed on an intention-to-treat basis.

### Study data

#### Data management

Data will be managed using the InferMed MACRO database system. An electronic case report form (eCRF) will be created using the InferMed Macro system. This system is regulatory compliant (GCP, 21CRF11, EC Clinical Trial Directive). The eCRF will be created in collaboration with the trial statisticians and the chief investigator (CI) and maintained by the King's Clinical Trials Unit. It will be hosted on a dedicated secure server within KCL. Source data will be entered by authorised staff onto the eCRF with a full audit trail.

#### Database passwords

Database access will be strictly restricted through passwords to the authorised research team. The CI or delegate will request usernames and passwords from the KCTU. It is a legal requirement that passwords to the eCRF are not shared, and that only those authorised to access the system are allowed to do so. If new staff members join the study, a personalised username and password will be requested via the CI or delegate.

#### Identifiable data

All participant contact information data will be stored on spreadsheets within the recruiting NHS site, which will have restricted access from password protected computers. Accrual data uploaded to the UKCRN portfolio database will be anonymised and collated by the CI or delegate to the CLRN. No identifiable data will be entered on the eCRF or transferred to the KCTU. Participants will be identified on the study database using a unique code and initials. The investigator will maintain accurate patient records detailing observations on each patient enrolled.

### Statistical methods

#### Primary analysis

If the study continues to full recruitment, analyses of effectiveness will be pragmatic, based on the intention-to-treat (ITT) sample. The significance level will be 5% (two-sided) for specified analyses. The estimated effect size and its precision (95% CIs) will be presented for all outcomes. The main statistical analyses will establish the effectiveness of IVIG against standard therapy at 6 months postrandomisation (see primary end points above). To this end, linear mixed modelling (LMM) will be employed. In such models, the binary outcome variable measured at the post-treatment time points (3, 6 or 12 months) features as the dependent variable with outcome at baseline (if applicable), stratification factors (service level), treatment arm and a treatment x time interaction term included as covariates. To account for correlation between repeated measures on the same individual, a subject-varying random intercept will be included. Mixed effects logistic regression can be completed using the ‘*xtmelogit’* command in Stata.

There are expected to be some missing data in the post-treatment outcome variables. The LMM analyses are based on maximum likelihood and will provide valid inferences under a missing at random (MAR) missingness mechanism.

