## Introduction

Transverse myelitis (TM) is a rare inflammatory disorder of the spinal cord affecting approximately 350 children and adults annually in the UK.^1^
^2^ Histologically, TM is characterised by spinal cord immune cellular infiltration, and pathogenesis is mediated by a variety of immunological mechanisms.^3^ Clinical features include a rapid onset of motor, sensory and autonomic dysfunction, and a prolonged recovery phase which may continue for up to 4 years.^4^ Diagnostic criteria for TM were established by the TM Consortium Working Group in 2002, to distinguish TM from other conditions including MS and a clinically isolated syndrome.^5^ A proportion of patients initially diagnosed with TM will subsequently relapse, often with involvement of other parts of the central nervous system, and may often be diagnosed with either multiple sclerosis (MS) or neuromyelitis optica (NMO). However, a proportion of patients remain as relapsing TM of as yet unknown aetiologies.

NMO is a relapsing subset of TM, caused by antibodies to aquaporin-4, an astrocytic water channel.^6^ Clinically, patients have predominantly recurrent episodes of myelitis and optic neuritis. Initial presentation may be with myelitis alone, making it clinically and radiologically indistinguishable from TM, and patients are thus subjected to the same acute therapeutic strategies.

The American Spinal Injury Association (ASIA) international standards for neurological classification of spinal cord injury enables a standardised assessment of neurological outcome, where A is no sensory or motor function in S4–5, and E is normal function.^7^ Retrospective data from paediatric cohorts suggest that 30% have ASIA A-C or expanded disability status scale (EDSS) ≥4 after TM,^8^ and a retrospective French multicentre study in adults found that 36% had a poor prognosis as defined by death or non-ambulatory status with current therapy.^9^ Since this is primarily a disease of younger people, this results in significant cumulative demands on health and social care resources.

There are no robust controlled trials in children or adults to inform on the optimal treatment of TM. Standard treatment with intravenous methylprednisolone (IVMP) is based on class IV evidence that it shortens relapse duration and speeds recovery in exacerbations of adult multiple sclerosis.^6^

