#### Primary outcome measure

A two point or greater improvement in the ASIA scale (classified A-E) at 6 months postrandomisation, when compared to baseline, will indicate a positive outcome.

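### Read literally, the primary model has no usable baseline severity term: the baseline value of the responder indicator is 0 for everyone, and entry ASIA grade is not named as a covariate

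*Protocol article*

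**What the plan says.** All references are to the protocol article.

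- **Endpoint.** Under Primary outcome measure, success is "A two point or greater improvement in the ASIA scale (classified A-E) at 6 months postrandomisation, when compared to baseline".
- **Scale and entry.** The Introduction describes the scale as one "where A is no sensory or motor function in S4–5, and E is normal function". The inclusion criteria admit grades A to C only. Table 1 shows the grade recorded at T0 for every participant.
- **Model.** Under Primary analysis, "the binary outcome variable measured at the post-treatment time points (3, 6 or 12 months) features as the dependent variable". The covariates follow: the binary outcome "features as the dependent variable with outcome at baseline (if applicable), stratification factors (service level", with "treatment arm and a treatment x time interaction term included as covariates". A random intercept per participant is added.
- **Randomisation.** Allocation uses "stratified block randomisation by service type (adult or child", with no other stratification factor.
- **Sample size.** The assumed response rates are "approximately 0.5 (50%) in the control arm and a minimum of 0.75 (75%) in the intervention arm", with no baseline adjustment mentioned.

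**The concern.** The covariate list contains one term meant to carry baseline information about the outcome. For a change-from-baseline responder indicator that term is a constant. An analyst who follows the sentence as written will treat it as not applicable and fit a model whose only baseline covariate is adult or child service.

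Yet the event being modelled differs by entry grade. Grade A responds by reaching C or better, grade B by reaching D or better, and grade C only by reaching E, which is normal function. If response probability differs materially across these transitions, leaving grade out gives up precision that data already collected would supply. It also leaves the estimate exposed to chance differences between arms in grade mix, because allocation does not balance grade.

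There is a further consequence for missing data. The plan relies on a missing-at-random assumption, and the Economic analysis section ties this to missingness being predicted only by variables in the model. With 10% attrition expected, that argument is weaker if dropout depends on entry severity and severity is not in the model.

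**Working it through.** **1. The plan's own figure.** Inputs from Sample size: 0.50 versus 0.75, two-sided 5%, 90% power. Pooled-variance formula:

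n = [1.960·√(2·0.625·0.375) + 1.2816·√(0.5·0.5 + 0.75·0.25)]² / 0.25² = (1.342 + 0.848)² / 0.0625 ≈ 76.7 per arm.

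The stated 76 gives power 0.897, and 76/0.9 rounds up to 85 per arm, or 170. The figure reproduces, and it involves no baseline covariate.

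**2. What the baseline term equals.** Improvement at time t is the grade at t minus the grade at T0. At t = T0 this is 0, so the indicator of a two-grade improvement is 0 for all. A constant cannot be estimated separately from the intercept.

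**3. What adding entry grade does to power.** The documents give no grade mix and no grade-specific response rates, so both are assumptions. Logistic regression at 6 months, 76 per arm, 2,000 simulated trials per row, marginal rates held at 0.50 and 0.75, a common odds ratio across grades, both models fitted to the same data:

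| Mix A/B/C (%) | Control response A/B/C | Power without grade | Power with grade | Change (points) |
|---|---|---|---|---|
| equal thirds | 0.50/0.50/0.50 | 0.905 | 0.897 | -0.8 |
| equal thirds | 0.35/0.50/0.65 | 0.905 | 0.913 | +0.8 |
| 30/20/50 | 0.40/0.85/0.42 | 0.903 | 0.920 | +1.7 |
| 25/25/50 | 0.20/0.70/0.55 | 0.892 | 0.920 | +2.8 |
| equal thirds | 0.20/0.50/0.80 | 0.897 | 0.951 | +5.4 |

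The Monte Carlo standard error of each power is √(0.9·0.1/2000) ≈ 0.7 point. Under no treatment effect, type I error was 0.035 to 0.050 without grade and 0.043 to 0.056 with it.

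Three further scenarios with half the patients in grade C (3,000 trials each) fit this pattern: 0.65/0.60/0.38 went from 90.6% to 91.6%, 0.75/0.60/0.30 from 89% to 93.5%, and 0.15/0.45/0.70 from 89% to 95% (89–91% to 95% on repetition).

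**4. Chance imbalance.** The SD of the between-arm difference in the share of one grade is √(2p(1−p)/76).

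- With p = 1/3: 7.6 points, and a difference above 10 points has probability about 19%.
- With p = 1/2: √(0.5/76) = 8.1 points, so 2 SD is 16.2 points, reached in about 5% of trials.

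Take mix 30/20/50 and control response 0.75/0.60/0.30.

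- Control gap between non-C and C: (0.3·0.75 + 0.2·0.60)/0.5 − 0.30 = 0.69 − 0.30 = 0.39.
- With an odds ratio of about 3.6, treated rates are 0.915/0.844/0.607, so the treated gap is 0.887 − 0.607 = 0.28.
- Splitting the 16.2 points evenly between arms: 0.081·0.39 + 0.081·0.28 = 0.054, or 5.4 points.
- Standard error of the unadjusted difference: √((0.25 + 0.1875)/76) = 0.076, or 7.6 points.

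The shift is about 0.7 of a standard error.

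**5. Effect on the odds ratio.** In the five tabulated scenarios the median estimated odds ratio was about 3.0 to 3.1 without grade and 3.1 to 4.2 with it. Adjustment changes what the ratio is conditional on.

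**The case against.** The strongest objection is that the authors may already have meant entry grade. Outcome measures names the ASIA Impairment scale itself as the primary outcome measure, and Secondary analyses adjusts for the baseline value of each measure. On that reading the plan contains the adjustment sought here. This stands in part: a reader might infer that the model certainly omits severity, and the text does not support that. It supports only that the stated list does not fix the matter.

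A second objection is that this is a condensed article that refers readers to the full protocol and an appendix for analysis detail. That would answer a complaint about missing detail. Here, however, the article does list the covariates, and one of them is empty when taken at its word.

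A third is that randomisation makes the test valid without grade. This stands in full. A reader might infer bias, an inflated type I error or a wrong sample size; neither the documents nor the simulations show any of these.

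A fourth is that nothing in the documents shows grade to be a strong predictor. This also stands. That grade sets the required transition does not show that response rates differ much, and the Secondary objectives treat early predictors as still to be identified. The assumed scenarios even run in opposite directions.

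Finally, the simulations use one time point. The planned mixed model has repeated measures and a random intercept, so its odds ratio is already conditional on the participant, and neither the power gain nor the change in odds ratio need carry over at the same size.

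**Conclusion.** The point holds as a low-cost improvement and a needed clarification, not as a flaw that invalidates the analysis. On the literal text no usable severity term enters the primary model or the randomisation; on a looser reading one does, and analysts could defend either.

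If grade is left out, the loss ranges from nothing to about 5 points of power, and where grade is not prognostic, including it costs under 1 point. The imbalance shift of about 5 points belongs to a strongly prognostic scenario and an uncommon draw. It is smaller than one standard error and is ordinary sampling variation, which adjustment would reduce; it should not be read as bias. All these sizes depend on assumed grade mixes and response rates. The missing-data consequence applies only if dropout is related to entry severity, which the documents do not address.

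**What to change.** Under Primary analysis, for the primary outcome, replace the generic baseline-outcome term with *baseline ASIA impairment grade (A, B, C; categorical)*, kept alongside service type. Add that the treatment odds ratio is conditional on these covariates. Optionally, also report a standardised risk difference, which is on the same scale as the 25-point difference in Sample size. Make the change before treatment groups are unblinded for the final analysis.

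The cost is a line or two of wording. Grade is already recorded at T0, so there is no new data collection, no change to randomisation and no change to the sample size. The one substantive consequence is the interpretation of the odds ratio, which the added statement covers. If entry grade was the intended meaning all along, the same wording simply makes that explicit.

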#### Secondary analyses

The secondary clinical assessments (EDSS, ASIA motor and sensory scales, SCI data sets, PedsQL, EQ5D and CSRI) with repeated measurements will also be analysed within a LMM framework where generalisations of the LMM will be utilised to allow for outcomes with non-normal data if necessary. Those measures with one follow-up assessment will be evaluated with in a Generalised Linear Model. The dependent variable will feature as the outcome measure. The covariates will be the corresponding baseline measure (if applicable), stratification factors and treatment group.

#### Exploratory moderator analyses

All analysis will be repeated considering age status (adult or child) as a moderator in interaction with the treatment group (control or intervention), allowing estimates of treatment effect in the subpopulations to be summarised.^23^ We will carry out further explanatory analyses to assess the efficacy of the treatment within NMO or idiopathic TM diagnosis and further putative biological markers by allowing for interactions with the treatment arm. When considering these moderator analyses, following established methods^24^ we will centre and orthogonalise interaction terms.

Further information on the statistical analysis plan can be found in the protocol and online supplementary appendix 1.

#### Interim futility analysis

TM is a rare disease and therefore requires a multicentre trial spanning several years, precluding recruitment to other interventional studies for this cohort. As such, an interim futility analysis will be performed after a 6-month follow-up of 52 patients. If sample sizes are equal, the trial may be abandoned if the successes in the intervention group are fewer than in the standard group. The probability of abandoning the study at the interim analysis is 0.4449 if there is no difference between treatment groups, and 0.0201 if treatment improves outcome. The primary trial statistician will remain blinded to the intervention and control groups, and therefore an additional unmasked trial statistician will perform the interim analysis. The results will be reviewed by the Data Monitoring Committee, which has the ability to terminate the trial prematurely.

### Economic analysis

Drug pricing data and primary care, secondary care and social care costs will be calculated as previously described. Costs will be combined with the primary outcome measure in the form of a cost-effectiveness analysis. If IVIG results in higher costs and better outcome, then an incremental cost-effectiveness ratio will be generated to show the extra cost incurred to achieve an extra unit of improvement. Owing to the uncertainty around results, cost-effectiveness planes and cost-effectiveness acceptability curves will be used, with bootstrapping of skewed results.

Long-term cost-effectiveness over 5-year and 10-year periods will be calculated using a Markov model. Response to treatment will be classified, and transition probabilities between groups will be derived from 6-month and 12-month follow-up data. Costs and QALYs for each category will be derived from the trial data. As limited data will be available on long-term costs, we will conduct both deterministic and probabilistic sensitivity analyses.

All causes of withdrawal from randomised treatment will be reported. χ^2^ (Fisher's exact test) will be used for categorical outcomes (eg, serious adverse events and mortality).

There will be missing data in post-treatment outcome variables as participants discontinue treatment or are lost to follow-up. Inferences will be valid provided the missing data generating mechanism is missing at random (MAR), and is not predicted by any variables in the model, that is, missingness is predicted only by variables that are included in the model.

### Economic evaluation

The use of IVIG, IVMP, additional treatments and rescue PLEX will be recorded throughout the follow-up period and costed using drug pricing data from the British National Formulary and the Department of Health. Use of primary care, secondary care and social care will be recorded at three-month, 6-month and 12-month follow-ups using the CSRI, and costs calculated to determine total cost for THE control and treatment arms.

A cost-effectiveness analysis will be performed using the primary and secondary outcome measures of improvement in ASIA scores, and secondary outcome of QALYs with EQ-5D-Y, EQ-5D-5L and CSRI. If IVIG results in higher costs and better outcome, then an incremental cost-effectiveness ratio will be generated to show the extra cost incurred to achieve an extra unit of improvement.

### Data monitoring

The Data Monitoring Committee (DMC) will review effectiveness and safety data during the trial to inform their recommendations to the Trial Steering Committee (TSC). The DMC is independent from the sponsor and funders, and will consist of a statistician, a clinician and a clinician scientist.

### Harms

Most adverse drug reactions that occur in this study, whether serious or not, will be expected treatment-related side effects as IVIG has a well-established side effect profile. Monitoring and reporting of adverse events will be performed by the site PI and research team, and will be recorded on an eCRF and uploaded to the InferMed MACRO database. Serious adverse events will be reported expeditiously to the sponsor, who in turn will inform the CI. The CI will assess SUSAR status. If a SUSAR is detected, the CI will work with the sponsor to report to the regulatory authorities. The CI will report to the relevant ethics committees and DMC.

An independent TSC and DMC will convene every 6 months; the TSC's key purpose will be to monitor study progress and act on the recommendations of the DMC. The DMC will aim to meet 3 weeks prior to the TSC convening. Additional meetings will be arranged if recommended by the DMC or TSC.

